**Figure 2 F2:**
[figure not shown]
The postures of *TCPSQ*. (A) The circle of between the hands. (B) The circle of arms. (C) The circle of arches of the feet. (D) High postures of *TCPSQ*. (E) Medium postures of *TCPSQ*. (F) Medium postures of *TCPSQ*.

#### Control group

2.11.2

The participants in the control group will not receive any specific training. They will be informed to maintain their original daily lifestyle in the intervention period (based on the initial inclusion criteria that they were not exercising on a regular basis) and requested not to commence any regular exercise regime or participate in other mind-body exercises, such as yoga or other forms of Qigong. On the completion of the study they will be given the same 10 weeks of *TCPSQ* training after the 19 weeks so as to increase involvement compliance rate.

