### Study objective and hypotheses

2.1

The primary aim of this RCT will be to systematically evaluate the effectiveness and safety, feasibility of *TCPSQ* on physical and psychological health of college students by observing the difference between the *TCPSQ* group and unaltered lifestyle control group.

The primary hypothesis of this study is that college students who receive a 10-week *TCPSQ* training intervention will show greater improvement in physical and psychological health than those who keep to their usual daily lifestyle, as assessed immediately after the 10-week training intervention, and these benefits will continue until the end of 8-week follow-up.

The secondary aims of this study are:

1.To investigate if *TCPSQ* is more beneficial to biomechanical balance and morphological balance of spinal in college students than usual daily lifestyle.2.To investigate the effect of *TCPSQ* on specific domains of breathing degree and heart activity in college student.3.To explore the mechanism of action of *TCPSQ* on psychological health in college students based on electroencephalogram and psychological self-rating scales.4.To verify whether the gains in both physical and psychological capacities related to balance and mobility and quality of life of college students trained by *TCPSQ.*

We hypothesis that college students with subhealthy state who receive a 10-week *TCPSQ* training intervention will achieve greater improvement in specific domains of spinal balance, breathing degree, heart activity, and show favorable changes in function of related brain regions than those who maintain their usual daily lifestyle.

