In order to exclude bias from the exceed activity of participants, all participants in both groups will be required to record PA diaries, including the type and intensity of physical activity or exercises, as well as the sedentary time and sleeping time everyday throughout this study.

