### Follow-up period

2.12

During the 8-week unsupervised follow-up period, all of the participants will return to their original lifestyles. But all participants will be required to record their daily physical activities or sport information. The forms will be returned to the researchers for following up each day by email or mail.

A weekly gathering will be organized for discussion of health-related topics and detailed follow-up.

The physical and psychological self-reported scales will be re-evaluated at the end of follow-up period. The follow-up assessment is designed to evaluate the long-term effect of *TCPSQ* on physical and psychological health of college students.

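### The request not to start other exercise goes to controls only, so other exercise taken up in the TCPSQ arm during the 10 weeks could be credited to TCPSQ

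*Protocol article*

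**What the plan says.** All references are to the protocol article.

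- **Controls (2.11.2).** "They will be informed to maintain their original daily lifestyle in the intervention period", and they are also "requested not to commence any regular exercise regime or participate in other mind-body exercises, such as yoga or other forms of Qigong". They are offered TCPSQ training only after week 19.
- **TCPSQ arm (2.11.1 and 2.11.3).** The posture, workshop, session timetable, self-evaluation scale and compliance measure are described. Nothing is said about starting other exercise.
- **Both arms (end of 2.11.3).** "In order to exclude bias from the exceed activity of participants, all participants in both groups will be required to record PA diaries", every day and for the whole study.
- **Follow-up (2.12).** "all of the participants will return to their original lifestyles", with daily activity records and a weekly gathering on health topics.
- **Hypotheses (2.1).** The comparison is with students who hold to their habits: "than those who keep to their usual daily lifestyle, as assessed immediately after the 10-week training intervention" for the primary hypothesis and "than those who maintain their usual daily lifestyle" for the secondary one.
- **Analysis (2.16).** Training logs feed the adherence models. No use of the activity diaries is stated.

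**The concern.** The article lays down a rule on additional exercise and addresses it to one arm. Read as written, a control who takes up running or yoga goes against a request, while a TCPSQ participant who does the same does not. Neither participants nor coaches are blinded (2.10), and only the TCPSQ arm attends a workshop on the health benefits of the practice (2.11.3). A difference in uptake is therefore plausible, although its size is unknown.

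Other exercise can act on the same outcomes as TCPSQ: balance, anxiety and depression among the primary outcomes, and blood pressure, heart rate and sleep among the secondary ones. Any improvement it brings in the TCPSQ arm would be attributed to TCPSQ at weeks 6 and 11. Exercise prompted by TCPSQ might be regarded as part of its effect, but that argument needs a control arm equally free to start, and here controls are asked not to.

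**Working it through.** **Step 1. Compare the rules by arm and period.**

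| | Controls | TCPSQ arm |
|---|---|---|
| Start other exercise, intervention | Asked not to (2.11.2) | No request stated (2.11.1, 2.11.3) |
| Activity diary, intervention | Yes (2.11.3) | Yes (2.11.3) |
| Follow-up condition | Original lifestyle (2.12) | Original lifestyle (2.12) |
| Activity record, follow-up | Yes (2.12) | Yes (2.12) |

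The arms differ only in the first row.

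**Step 2. See whether another section closes the gap.** The exclusions in 2.6 (long-term Qigong or athletic practice, membership of certain clubs) govern entry, not uptake after randomisation. The withdrawal criteria in 2.7 name controls who regularly practise TCPSQ; they do not mention other exercise in either arm. The diaries measure activity without restricting it. None of these supplies the missing request.

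**Step 3. Size.** The article gives no figure on this point, so there is none to reproduce. Assumed inputs: a difference in uptake between arms of 10% to 30%, with almost none among controls, and an effect of the other exercise of 0.3 to 0.5 SD.

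Bias = difference in uptake × effect of the other exercise

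- Low: 0.10 × 0.3 = 0.03 SD
- Middle: 0.20 × 0.3 = 0.06 SD to 0.20 × 0.5 = 0.10 SD
- High: 0.30 × 0.5 = 0.15 SD

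**Step 4. Set this against the trial's resolution.** Section 2.3 names 30 per group as the minimum. With a two-sided 0.05 level (2.16), an assumed power of 80% and the normal approximation:

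Detectable difference = (1.960 + 0.842) × √(2/30) = 2.802 × 0.258 = 0.72 SD

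The bias is thus about 4% (0.03/0.72) to 21% (0.15/0.72) of that difference.

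**Step 5. Consequence for the next trial.** Section 2.3 says the pilot is to serve sample-size planning, and the Discussion says effect sizes will be compared for that purpose. Suppose the pilot shows 0.50 SD (assumed). With n per arm = 2 × 2.802² / d² = 15.70 / d²:

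- d = 0.50, as observed: 15.70 / 0.2500 = 62.8, so 63
- d = 0.47, after removing 0.03: 15.70 / 0.2209 = 71.1, so 72
- d = 0.35, after removing 0.15: 15.70 / 0.1225 = 128.2, so 129

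Under these assumptions, a bias that is hard to see in the pilot could leave the later trial short by 9 to 66 per arm.

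**The case against.** **The gap is silence in a condensed article.** Section 2.11.3 says TCPSQ participants are told about study procedures and matters needing attention, and a matching request could be given there. This is fair, and it means one cannot say that the TCPSQ arm is permitted to add exercise. But the article did choose to print the rule, and printed it for one arm in a section that applies to that arm alone. As it stands, the published text describes a difference between the arms.

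**The risk is already handled.** The entry criteria remove many exercisers, and the diaries make added exercise measurable by arm. This stands in part: the data needed to judge the problem will exist. Recording is still not the exclusion of bias that 2.11.3 sets as its aim.

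**The size is unanchored and small.** This stands. The inputs are assumptions, and the direction depends on controls following the request. The 0.03-0.15 SD matters mainly because the pilot's estimates are to be carried forward.

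**Two stronger readings do not hold.**

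- A reader might infer that the restriction makes the comparator something other than the one in the hypotheses. Section 2.1 speaks of students who keep to or maintain their habits ("than those who keep to their usual daily lifestyle"). Asking students not to start a new regime carries that out, so the comparator in 2.1 needs no new label.
- A reader might infer that controls are released at week 11 and that the week-19 comparison is against a different control condition. In 2.11.2 the time limit belongs to the clause on maintaining lifestyle; the request not to start exercise has no end date of its own. Section 2.12 then puts all participants on their original lifestyles. Nothing says that controls may start exercising. The text merely leaves open whether the request continues.

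**Conclusion.** The point holds in a limited form. The request not to start other exercise is stated for controls only, no equivalent is stated for the unblinded TCPSQ arm, and the diaries neither restrict other activity nor have a stated place in the analysis. Followed as written, the plan could credit other exercise to TCPSQ at weeks 6 and 11.

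The likely size is about 0.03-0.15 SD in favour of TCPSQ. It rests entirely on assumed uptake (10-30% against almost none) and an assumed effect (0.3-0.5 SD). It would shrink, or could reverse, if controls disregarded the request. This does not undermine the trial, but it is an avoidable difference between arms in a study whose effect estimates are meant to be reused. For weeks 11 to 19 the documents support only a need for clarification.

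**What to change.** 1. State one request for both arms in 2.11: during the intervention, start no new regular exercise or mind-body practice. For the TCPSQ arm, add that the TCPSQ sessions are the only exception.
2. In 2.12, say whether the request continues to week 19. If it does, word it to agree with the return to original lifestyles. Simply extending to week 19 an exception for the allocated programme would imply that TCPSQ practice goes on during follow-up, which conflicts with that section.
3. Report diary-recorded other exercise by arm, separately for the intervention and follow-up periods, beside the primary results.

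The cost is small: one more instruction to the TCPSQ arm, a change of wording in the protocol and participant instructions, and one extra descriptive table. The activity records already exist in both arms, so no new data collection is needed.

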#### Intervention regimen

2.11.3

*TCPSQ* training consisted of an initial workshop conducted over 3 consecutive half-days by 2 qualified coaches. Participants received concentrated training: this consisted of instruction in source of *PSQ*, understanding in the essence and beneficial effects of *PSQ*. Participants will be taught the relevant knowledge of *TCPSQ*, which includes the rationale that *TCPSQ* constitutes a health benefit, the action essence of *TCPSQ* the philosophy opinion of *TCPSQ*. The instruction of *TCPSQ* will be both verbal and visual. And participants will be also obtained information about procedure of this study, and the matter needing attention of individuals in the trial. Participants will be required to learn the key movements known as “regulating body, breathe, mind” and ancillary exercises with multiple repetitions of *TCPSQ* until they master it, as will be confirmed by the professional coaches. The coaches will visit each individual daily to ensure that the movements are being correctly practiced.

Once initial concentrated training was complete, participants were asked to practice supervised training. Participants of *TCPSQ* group will undergo the regular training together for the last 10 weeks at a frequency of 5 days per week (from Monday to Friday), training will be performed for 50 minutes per day, each session will include a warm-up for 10 minutes. Specified *TCPSQ* performed and refined for 30 minutes, the practice method successively as follows: body adjustment; breathing adjustment; mind adjustment, and cooling down for 10 minutes. The instructors will visit each individual to ensure that the movements are being correctly practiced. All participants will be required to fill self-made *TCPSQ* training self-evaluation scale (including self-evaluation of training difficulty, the relaxation or tensity or pain and fatigue of various parts of body, perspiration level, saliva secretion level, body sense of warmth, breathing control state, meditative state of mind, abnormal physical and mental reaction, level of coordination between body and mind during and after training) and record their daily PA information during the intervention period. The compliance of the subjects will be assessed in terms of the number of training attended and the number of training self-evaluation scale per day.

In order to exclude bias from the exceed activity of participants, all participants in both groups will be required to record PA diaries, including the type and intensity of physical activity or exercises, as well as the sedentary time and sleeping time everyday throughout this study.

### Follow-up period

2.12

During the 8-week unsupervised follow-up period, all of the participants will return to their original lifestyles. But all participants will be required to record their daily physical activities or sport information. The forms will be returned to the researchers for following up each day by email or mail.

A weekly gathering will be organized for discussion of health-related topics and detailed follow-up.

The physical and psychological self-reported scales will be re-evaluated at the end of follow-up period. The follow-up assessment is designed to evaluate the long-term effect of *TCPSQ* on physical and psychological health of college students.

### Outcome assessment

2.13

Outcome measurements consist of basic characteristics of information, bioelectrical activity of cortical neurons, biomechanical balance of spinal column (dynamic and static), morphological balance of spinal column, degree of thoracic breathing and abdominal breathing, electrical activity of the heart, cardiopulmonary function, as well as self-reported symptom intensity, anxiety, depression, personality, self-esteem, quality of sleep, constitution in Chinese medicine, symptoms induced by spinal problems, and self-evaluation of Qigong training. The basic characteristics of information will be collected at baseline (1–2 weeks before randomized allocation). The relevant primary and secondary outcomes will be assessed at baseline, 6 weeks (at the mid-point of intervention), 11 weeks (at the end of intervention), and the physical and psychological self-reported scales measurement will be assessed at 19 weeks (after the 8-week follow-up period). Bioelectrical activity of cortical neurons, biomechanical balance of spinal column (dynamic and static), morphological balance of spinal column, degree of thoracic breathing and abdominal breathing, electrical activity of the heart, and cardiopulmonary function will be assessed at the Qigong and Human Science Laboratory of BUCM by experienced operators who are not otherwise involved in this study. Several outcome assessors who are incharge with the physical and psychological self-reported scales measurement will investigate the physical and psychological status of the participants (such as Symptom Checklist-90 [SCL-90],^[90]^ Self-Rating Anxiety Scale [SAS],^[91]^ Self-rating Depression Scale [SDS],^[92]^ Eysenck Personality Questionnaire-revised, Short Scale for Chinese [ EPQ-RSC],^[93,94]^ Rosenberg Self-esteem Scale [RSES],^[95]^ Pittsburgh Sleep Quality Index [PSQI],^[96]^ Constitution in Chinese Medicine Questionnaire [CCMQ],^[97]^ Self-made Questionnaires of Symptoms Induced by Spinal Problems (SQSSP), Self-made Qigong Training Self-evaluation Scale [SQTSS]) at college student activity center. A summary of all measures in the trial is shown in Table 1.

**Table 1 T1:**
[figure not shown]
Trial measures processes chart.

#### Basic characteristics variables

2.13.1

Demographic characteristics information of each participant's sex, age, nationality, native place, marital status, handedness, height and weight, medical history, family history of disease will be collected by the recruiters using the Self-designed Standardized Questionnaire (SSQ) at baseline. Lifestyle factors, including diet, physical activity or exercise habits, smoking habit, and drinking alcohol habit, will also be recorded. Baseline assessment will be completed before randomization.

#### Primary outcomes

2.13.2

Primary outcomes consist of bioelectrical activity of cortical neurons, biomechanical balance of spinal column, morphological balance of spinal column, degree of thoracic breathing and abdominal breathing, electrical activity of the heart, as well as self-reported symptom intensity, anxiety, depression.

1.Bioelectrical activity of cortical neurons including electroencephalograph power spectrum of δ, θ, α1, α2, β1, β2 in *TCPSQ* state and natural stance state. It will be assessed by *the Nuamps 40 channel electroencephalograph (EEG) signal recording and analysis system and the curry-7 acquisition software* produced by Neuroscan Company, United States.2.Biomechanical balance of spinal column including static biomechanical balance of spinal column and dynamic biomechanical balance of spinal column. Static biomechanical balance of spinal column consists of average value of foot plantar pressure, peak value of foot plantar pressure, foot contact area, center value of foot plantar pressure, center-of-gravity path, balance function index (such as vacillation range, envelope area of posturography, average barycentric coordinates, and so on) during *TCPSQ* state and natural stance state, as well as single foot and closed eye state, single foot and open eyes state. Dynamic biomechanical balance of spinal column consists of dynamic impulse in double feet, walking speed and acceleration, height change of the body's center of gravity, ground reaction force, foot pressure center track, average value of foot plantar pressure, peak value of foot plantar pressure, and foot contact area during the natural walking. It will be tested via *the Footscan Balance 7.7 acquisition and recording system and the Free STEP V.1.5.01 analysis software* produced by Sensor Medical Company, Italy.3.Morphological balance of the spinal column consists of sagittal physiological curvature of spine, total flexion-extension activity, flexion activity, extension activity, coronal physiological curvature of spine, total left flexion-right flexion activity, left flexion activity, and right flexion activity. It will be detected with *the Spinal-mouse Spinal morphology measuring instrument* produced by Idiag, Switzerland.4.Degree of thoracic breathing and abdominal breathing, electrical activity of the heart will be measured by *the MP150 multiple-channel electrophysiological recording device* produced by Upwards Teksystems Ltd., United States.5.SCL-90 will be used to measure symptom intensity, which consists of the following 10 symptom factors: somatization, obsessive-compulsive disorder, interpersonal sensitivity, depression, anxiety, hostility, phobic anxiety, paranoid ideation, psychoticism, and other.^[90]^6.Anxiety will be measured with SAS. The scale consists of 20 questions that reflect subjective feelings of anxiety symptoms. Participants are asked to respond to each question on a 4-point Likert scale ranging from 0 (never or few time) to 3 (very often or whole time). Higher composite scores indicate greater anxiety.^[91]^7.Depression will be measured with SDS. 20 questions in SDS that reflect subjective feelings of depression symptoms. Participants are asked to respond to each question on a 4-point Likert scale ranging from 0 (never or few time) to 3 (very often or whole time). Higher composite scores indicate greater depression.^[92]^

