**Discussion::**

This is the first randomized controlled trial protocol from the perspective of Qigong connotation to systematically investigate the effect of *TCPSQ* for the physical and mental health of a college student population. If the results in our study prove a significant intervention effect, this would provide preliminary higher-quality evidence and establish an optimal guidance for the application of *TCPSQ* exercise program among a college student population.

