### Sample size

2.3

There are no previous clinical trials to explore the beneficial effect of *TCPSQ* on college students from the integrating with physical fitness and psychological well-being. Therefore, this study is designed as a pilot study to calculate the appropriate sample size for future randomized clinical trials. Each group should include 30 participants, which is the minimum sample size for evaluating the effect of *TCPSQ*. Considering a 20% attrition rate, a total of 80 participants are necessary, with 40 participants in each group.

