### Statistical analysis

2.16

Collected data will be recorded on standardized forms. Descriptive statistics will be calculated for dependent and independent variables. This analysis will include summary statistics of demographic information and outcome measures. Continuous variables will be summarized as mean (SD) ± standard deviation for normal distribution, and median (IQR) ± interquartile range for non-normal distribution. Normality will be tested using *Kolmogorov–Smirnov* test and categorical variables will be presented with frequencies or percentages. Appropriate transformations will be applied in cases of non-normal distribution. For the variables with a normal distribution, differences in terms of outcomes between groups will be compared using an independent *T-*test. If the variables have a non-normal distribution of ordinal level, statistical comparison between groups will be made by using the *Mann– Whitney U* test even after suitable transformations. Measures with a discrete distribution will be expressed as percentages and analyzed by the *X*^*2*^ or Fisher's exact test as appropriate. Subgroup analysis will be performed according to participants’ gender, personality, and constitution of TCM. Analysis of variance (ANOVA) will be used for the repeated measurement data, and *post-hoc* comparison between groups at different assessment time points will be conducted using multiple comparisons with adjustment to the type 1 error rate. Analysis of the primary and secondary outcomes will be on the basis of intention-to-treat (ITT) population and per-protocol (PP) population. The result of the ITT analysis will be compared with that of the PP analysis to check whether the results are consistent or not. If the statistical results of the ITT and PP population data are the same, the results will be deemed to be reliable; if they are contrary, we intend to adopt the results of the ITT population. The method of processing missing data will be the last observation carried forward (LOCF). This refers to assigning the last observed value of the end point indicator to the subsequent missing evaluation point; that is, the last observation response will be considered to be the study end point. Safety will be evaluated by tabulations of AEs, and will be presented with descriptive statistics for each group. A chi-square test or a Fisher's exact test will be used to compare the frequency difference in AEs between the 2 groups, and severe AEs will be listed in detail. To explore potential factors which might influence adherence, a logistic regression model and a linear mixed-effects model will be used and adjusted for potential confounders. Adherence-related data will be taken from training log records. All statistical tests will be implemented using IBM SPSS 21.0 with bilateral inspection. The level of statistical significance is assumed at 2-sided *P* value <.05.

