
Initially, one of strengths of this study is that strict, complete, randomization, and adequate concealment will be used in our trial. What is more, the extensive physical and psychological outcomes assessment on several levels involving bioelectrical activity of cortical neurons, biomechanical balance of spinal column morphological balance of spinal column, degree of thoracic breathing and abdominal breathing, electrical activity of the heart, cardiopulmonary function assessment will make it possible to explore the mechanism of action of *TCPSQ* which offer a comprehensive understanding on the adjustment of body, breath, and mind, allowing the researchers to investigate the relationship between subjective scales and objective indicators. At the same time, using the SQTSS to appraise training quality and effects of Qigong training on physiology, respiratory function and psychology from the perspective of participants themselves is also the unique highlight of this study.

The undeniable fact is that several potential limitations may occur in this protocol. Ideally, everyone involved in an RCT should be blinded, but this is not always feasible in the nonpharmacological trials,^[107]^ therefore performance bias may be inevitable. Although the participants and exercise coaches are not blinded and the psychological outcome measures are participants’ self-reported, the development of some form of sham intervention for use in future studies of Qigong is a desirable goal, and we will make every effort to ensure that outcome assessors, laboratory technicians, data managers, and statisticians are unaware of the treatment allocations and train the whole research team, inform the participants about the details of self-report scales. Second, all participants will come from one and the same medical university, which may decrease the sample representativeness. Third, limitations of this pilot study are the relatively small sample size (only 80 participants) because the sample size calculation process is not applied in this study. Thus we will compare the effect size between groups in order to form larger-scale trials and add subjective-objective quantitative indicators in future research.

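### Eight unranked primary domains share one 5% level with no adjustment across outcomes: the chance of a false primary finding is about 34% with one independent test per domain, and higher if components are tested separately

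*Protocol article*

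**What the plan says.** Section 2.13.2 lists the primary outcomes: "Primary outcomes consist of bioelectrical activity of cortical neurons, biomechanical balance of spinal column, morphological balance of spinal column", then "degree of thoracic breathing and abdominal breathing, electrical activity of the heart, as well as self-reported symptom intensity, anxiety, depression". That is eight domains, with no lead outcome, co-primary rule or testing order.

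The same section breaks the domains into components. The EEG domain is the "electroencephalograph power spectrum of δ, θ, α1, α2, β1, β2 in *TCPSQ* state and natural stance state". Static balance has several plantar-pressure measures and a "balance function index (such as vacillation range, envelope area of posturography, average barycentric coordinates, and so on", recorded in four stances. There are also a walking set, eight spinal-shape and mobility measures, ten SCL-90 factors, and the SAS and SDS.

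Section 2.16 chooses tests by type of variable (t-test, Mann-Whitney, chi-square, repeated-measures ANOVA) and closes with "The level of statistical significance is assumed at 2-sided" P below .05. The only adjustment of the type 1 error it mentions applies to post-hoc group comparisons at the different assessment times.

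Section 2.3 calls the study a pilot to size later trials, but also says "Each group should include 30 participants, which is the minimum sample size for evaluating the effect of" the intervention. Section 5 describes the 80 participants as appropriate, then lists the small sample as a limitation "because the sample size calculation process is not applied in this study". The Abstract says "If the results in our study prove a significant intervention effect", this would give preliminary evidence of higher quality and set guidance that it calls optimal. The end of section 5 repeats the thought in milder words.

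**The concern.** Section 2.1 states a confirmatory hypothesis: greater improvement in physical and psychological health right after the 10-week programme, lasting through follow-up. Nothing says which primary result, or how many, would confirm it. With eight primary domains each open to a 5% test, one favourable domain can be presented as the primary finding, and the article has already said what a significant effect would justify. The 5% level then no longer describes the risk of a false primary claim. The family is also not closed, because the list of balance indices ends open.

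**Working it through.** **The plan's own figure.** The only calculated number is the total of 80. Inflating 30 per arm for 20% attrition gives 30 / (1 − 0.20) = 37.5, so 38 per arm and 76 in total. Eighty is that figure rounded up to 40 per arm, which is harmless. The 30 itself cannot be reproduced, since no effect size, SD or power is given.

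**Inputs.**
- Domains (2.13.2): EEG, biomechanical balance, morphological balance, breathing, heart, symptom intensity, anxiety, depression = 8.
- Level (2.16): 0.05, two-sided.
- Correlations: none in the document, so all values below are assumptions.

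**Components, two ways of counting.**
- By name only: EEG 6 + static 6 (balance index counted once) + dynamic 8 + morphology 8 + breathing 2 + heart 1 + SCL-90 10 + SAS 1 + SDS 1 = 43.
- By name and measurement state: EEG 6 × 2 = 12; static 8 × 4 = 32 (three named index examples counted separately); dynamic 9 (speed and acceleration separate); morphology 8; breathing 2 × 2 = 4; heart 1 × 2 = 2; SCL-90 10; SAS 1; SDS 1. Total 79. The two states for breathing and heart come from the testing scheme in 2.13.3, not from 2.13.2.
- Intermediate readings give 67 to 76.

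**Chance of at least one P < .05 under no effect.** For m independent tests this is 1 − 0.95^m. The correlated figures come from simulated normal test statistics, 100,000 runs each, with one common correlation across all tests.

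| Tests | Independent | Common correlation 0.5 | Common correlation 0.7 |
|---|---|---|---|
| 8 | 1 − 0.95^8 = 33.7% | 25% | 19% |
| 43 | 1 − 0.95^43 = 89.0% | 59% | 38% |
| 79 | 1 − 0.95^79 = 98.3% | 73% | 46% |

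If variables are correlated within domains but not between them, the 79-test figure is 95%, 89%, 78% and 59% at within-domain correlations of 0.3, 0.5, 0.7 and 0.9. Expected false positives per visit are 8 × 0.05 = 0.4, 43 × 0.05 = 2.2 and 79 × 0.05 = 4.0. Several visits, the two analysis populations and three subgroup factors are not counted.

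**What the sample can detect.** Two-sample t-test, 30 per arm, 80% power: 0.74 SD at 0.05; 0.81 SD at 0.025 (first Holm step with two endpoints); 0.95 SD at 0.05/8 = 0.00625. For an assumed difference of 0.5 SD, power is 48%, 36% and 20% respectively. If attrition is exactly 20%, 40 × 0.80 = 32 per arm remain, and the first figure becomes 0.71 SD.

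**The case against.** The strongest reply has three parts.

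First, section 2.16 names generic tests and nowhere says that every component is a separate primary test. How components are summarised within a domain may be set out in an analysis plan that is not shown. This stands, and it is why the eight-domain figure leads. A reader might infer that a significant primary result is close to certain even if the intervention does nothing. The document does not support that. It would need about 79 independent tests, each read as primary, whereas the count multiplies names by state and the measures are plainly related: the same plantar pressures in several stances, total spinal motion beside its parts, and ten factors from one questionnaire. The reply does not remove the point, because choosing the primary outcome belongs in the protocol, and this text has chosen eight.

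Second, the trial is declared a pilot, and section 5 discloses both the missing calculation and the plan to use effect sizes for larger trials. This also stands. The absent calculation is an admitted limitation and not itself the defect. What remains is the wording that calls 30 a minimum for evaluating the effect and 80 appropriate.

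Third, a reader might take the Abstract to say that a significant result proves efficacy. It does not: the verb sits inside a condition, and the stated consequence is preliminary evidence. The narrower criticism is that optimal guidance claims too much for a pilot.

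**Conclusion.** The point holds. The primary hypothesis has no rejection rule, and the one adjustment in section 2.16 does not control error across outcomes. With one test per domain, the family-wise error is about 34% if the tests are independent and about 19% to 25% at common correlations of 0.7 to 0.5. With the 79 measure-by-state combinations tested separately it lies between roughly 46% and 98%. All of these are well above 5%. They rest on a global null, a 5% test for each member of the family, and assumed correlations. The 79-test range further assumes that components are tested one by one, which the text permits but does not state.

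**What to change.** Before any unblinding (under section 2.10, before the coded A/B allocation reaches the statistician), do one of the following.

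- Designate one or two primary variables at week 11. For example, take one psychological score already defined in 2.13.2, such as the SAS or SDS, and one named natural-stance balance index. If there are two, test them with Holm at an overall 0.05.
- Or keep the eight domains, prespecify one variable in each, and apply Holm across them at an overall 0.05.

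Move every other variable to secondary or exploratory, reported as estimates with 95% confidence intervals. In section 2.3, replace the statement about a minimum sample, and in section 5 the word appropriate, with the detectable difference: about 0.74 SD at 30 per arm, 80% power, two-sided 0.05, and larger under Holm. In the Abstract, drop the claim of optimal guidance in favour of pilot-level conclusions.

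The cost: fewer outcomes can be claimed as primary, and Holm lowers power per test (the detectable difference at the first step rises to 0.81 SD with two endpoints, 0.95 SD with eight). Section 3 requires a written application to the ethics committee for protocol changes, and the registry entry needs updating. No measurement, visit or participant number changes.
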